### Data management

Household data collected during the census and ITN follow up surveys will be captured on electronic forms using smartphones installed with OpenDataKit (ODK) Collect while entomological data will be recorded on data entry forms and double entered pre-designed excel data bases. Throughout the study, electronic data will be stored encrypted while paper forms will be locked up in secured cabinets and will be available only to study investigators and data management staff by passwords and keys. All personal data will be anonymized using a unique identifier number for each participant and household to ensure confidentiality. At the end of the study, all electronic files and data entry forms will be respectively stored on the server and archive of the CREC-LSHTM GLP certified facility for 10 years.

### Statistical analysis

Data from the surveys at 6, 12, 24, and 36 months will be used to calculate attrition, functional survival and median survival time using Kaplan–Meier estimators. For functional survival, nets reported as given away, sold, or stolen will be excluded from the analysis. Negative binomial regression will be used to compare hole surface area between the different ITN types. Data on WHO cone bioassays and tunnel tests will be obtained from 30 nets of each product type sampled at each time point. A chi-squared test will be used to assess the proportion of nets of each ITN type passing the WHO criteria for alphacypermethrin, chlorfenapyr and pyriproxyfen bioefficacy based on combined cone and tunnel tests. Proportional outcomes (mortality, blood-feeding, exophily) from the experimental hut trials will be compared at each time point using mixed effects logistic regression, with huts, sleepers, net replicate and nightly observational error included as random or fixed effects [33]. Numerical outcomes (hut entry) will be compared using negative binomial regression. A separate model will be fitted for each outcome to determine whether there is (i) a significant change over time, and (ii) a significant difference between ITNs washed 20 times and 36-month-old naturally aged ITNs. Analysis will be performed on STATA or the package *lme4* of the R software.

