### Follow up surveys for cohort 1 nets

#### Follow-up for ITN attrition

All households in cohort 1 (at least 750 nets/arm) will be visited at 6-, 12-, 24- and 36-months post ITN distribution and nets assessed for attrition at each timepoint by recording the physical presence/absence of each net that was marked in the household. Where a net is not found, the householder will be asked about the reason for the loss of the net, e.g. given away, sold, stolen, worn out and disposed of. Any net which has never been used, will be recorded, and excluded from the analysis. During these surveys, a questionnaire adapted from WHO guidelines will be used to collect data on the number of washes and washing practices for the nets found in each household.

ITN retention may also be affected by householders’ preference of the fabric type used in the formulation of the net. A low preference for polyethylene nets has been previously observed in Benin by the National Malaria Control Programme (NMCP), which may differentially affect the retention of Royal Guard^®^ (polyethylene) compared to Interceptor^®^ and Interceptor^®^ G2 (polyester). As part of these follow up surveys, a short questionnaire will be administered to assess householders’ perception of the ITN fabric types and changes in size of each ITN type to determine whether this may have impacted their decision to discard the net. A subset of ITNs of each type at 0, 12, 24 and 36-months post-distribution (minimum 100 per ITN type) will also be measured to directly examine changes in ITN size over time.

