### Sample size calculations

Sample size calculations are performed based on previous ITN durability data from Benin. For cohort 1, a sample size of 750 nets of each brand from 250 randomly selected households (assuming ~ 3 ITNs are distributed per household) in 5 study clusters was found sufficient to detect a 9.4% absolute difference (hazard ratio = 0.87) in ITN attrition rate assuming an attrition rate in the control arm of 70% over the 3 years and an intra-cluster correlation coefficient of 0.03. For cohort 2, a total of 522 ITNs will need to be withdrawn over three years and assuming a loss rate of 70% a total of 1800 ITNs will be marked per study arm at baseline. To reduce the impact of the durability study on the outcomes of the cRCT, cohort 2 nets will be obtained from households in the buffer areas of the selected clusters to exclude the core areas used for the cRCT sampling.

For each experimental hut trial and at each timepoint, data on the number of mosquitoes per night and the magnitude of the different random effects (huts, sleepers, nights and observational error) will be reviewed after the first round of 9 or 13 weeks and power calculations conducted by simulation using previously described methods [33]. Power analysis will determine whether the hut trial has a desired 80% power to detect superiority in mosquito killing of any new unused dual AI ITN over the new unused pyrethroid-only net, assuming a true underlying extra mortality from the dual AI net of 40%. A second round of hut trial would be performed if the desired level of power is not achieved.

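### Functional survival drops nets that were given away, sold or stolen instead of censoring them, which understates survival if such losses are unrelated to wear and can create a false gap between net types

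*Protocol article*

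**What the plan says.** The Statistical analysis section uses the cohort 1 surveys at 6, 12, 24 and 36 months to "calculate attrition, functional survival and median survival time using Kaplan–Meier estimators". The next sentence sets the rule at issue: "For functional survival, nets reported as given away, sold, or stolen will be excluded from the analysis". Censoring is not mentioned.

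The section Follow-up for ITN attrition describes what is recorded: whether each marked net is present at each visit and, for missing nets, why. "Where a net is not found, the householder will be asked about the reason for the loss of the net". No date of loss is mentioned. The same section notes that "A low preference for polyethylene nets has been previously observed in Benin", which "may differentially affect the retention of Royal Guard" relative to the two polyester nets.

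**The concern.** Functional survival is meant to describe how long a net stays usable, so it is right that a stolen or gifted net does not count as worn out. Removing it altogether goes further. A net found serviceable at 6, 12 and 24 months and given away before 36 months has shown at least 24 months of survival. Under the rule it contributes nothing at any time point. A net that wore out in its first months stays in as a failure. The analysis set is therefore selected on a later event, and nets that last longer have more time to be selected out. Using such partial follow-up is the purpose of the Kaplan–Meier method.

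Two results are at stake: the level of functional survival for each net, which the Discussion says will inform replacement and procurement, and the comparison between nets, which is the first study objective.

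**Working it through.** **Inputs.** The article states no figure for functional survival, so there is none to reproduce. The one input taken from it is 70% control-arm attrition over three years (Sample size calculations). The share of losses that are gifts, sales or thefts (*give-away* below) is not given and is varied. Assumed: constant hazards, and give-away independent of wear.

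**1. Bias in one arm.** Let s be the give-away share of losses. All-cause retention at 36 months is 0.30.
- True wear-only survival = 0.30^(1−s)
- Under deletion = 0.30 / (1 − 0.70s), because the fraction 0.70s of nets is removed

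| s | True | Deletion | Bias (points) |
|---|---|---|---|
| 10% | 33.8% | 0.30/0.93 = 32.3% | −1.6 |
| 20% | 38.2% | 0.30/0.86 = 34.9% | −3.3 |
| 30% | 43.1% | 0.30/0.79 = 38.0% | −5.1 |
| 50% | 54.8% | 0.30/0.65 = 46.2% | −8.6 |
| 70% | 69.7% | 0.30/0.51 = 58.8% | −10.9 |

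(Biases are from unrounded values.) At s = 20% the median interpolated between surveys falls from 26.2 to 23.2 months.

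**2. A milder deletion.** Suppose only nets already lost by each survey are dropped. At s = 50%, 12-month retention is 0.30^(1/3) = 0.669 and give-away to date is 0.331/2 = 0.165. The estimate is 0.669/(1 − 0.165) = 80.2%, against a true 81.8%. Full deletion gives 1 − 0.165/0.65 = 74.6%. At 36 months both readings give 46.2%.

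**3. False gap between arms.** Take true wear-only survival of 55% in both arms, so the wear hazard is Hw = −ln 0.55 = 0.598 over 36 months. Let g be the 36-month give-away risk in the absence of wear, with Hg = −ln(1−g). The fraction deleted is d = Hg/(Hw+Hg) × [1 − 0.55(1−g)], and the estimate is 0.55(1−g)/(1−d).
- g = 10%: d = 0.076, estimate 0.495/0.924 = 53.6%
- g = 30%: d = 0.230, estimate 0.385/0.770 = 50.0%
- g = 50%: d = 0.389, estimate 0.275/0.611 = 45.0%

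The false gap is 3.6 points for 10% vs 30% and 8.5 points for 10% vs 50%. It is zero when g is equal in both arms.

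**4. When give-away depends on wear.** Simulation with a frailty shared by wear and give-away (true survival 52.3%):
- More-worn nets given away, mild dependence: deletion 51.0% (−1.3), censoring 54.6% (+2.3)
- More-worn nets given away, strong dependence: deletion 53.3% (+1.0), censoring 55.2% (+2.9)

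If instead 20% or 40% of nets are given away within six months of wearing out (true 55.0%), deletion gives 60.2% or 66.6%, which is +5 to +12 points.

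**5. Where to censor.** Simulation with the four visits, independent give-away:

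| Censored at | s = 20% (true 38.2%) | s = 50% (true 54.8%) |
|---|---|---|
| Visit that detects loss | +1.3 | +2.8 |
| Previous visit | −1.1 | −2.7 |
| Actuarial (mid-interval) | within 0.2 | within 0.2 |

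**6. The survey dates themselves.** With no give-away, Kaplan–Meier at the visits reproduces the truth (81.8, 67, 44.8 and 30%). Only the median is affected: the true value is 36 × ln 2 / 1.204 = 20.7 months, but the step curve first falls below 50% at the 24-month visit.

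**The case against.** **The word may be loose.** In a condensed article, *excluded* could mean not counted as a failure, which would be censoring. That cannot be ruled out. However, the follow-up section uses the same expression for nets that were never used, where it can only mean removal, so removal is the natural reading. The abstract says standard WHO procedures are followed for attrition and fabric integrity. Those are not reproduced, and the effect of deletion on a Kaplan–Meier estimate is the same whatever its source.

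**The direction is not certain.** This stands. The downward bias needs give-away to be unrelated to wear. If households pass on their worst nets, deletion may do little harm or may overstate survival, and censoring is not unbiased either. This argues for a sensitivity analysis rather than for deletion.

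**The size is unknown.** This also stands, because the article gives no give-away share. At a 10% share the bias is small.

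**Stronger readings.** A reader might infer three things that the document does not support:
- *The protocol expects giving away to differ by net type.* It says that fabric preference "may differentially affect the retention of Royal Guard". Retention covers every kind of loss, and the section goes on to ask about decisions to discard, which is not one of the excluded reasons. Unequal give-away is plausible, but it is an inference.
- *The false gap can be set against the design difference.* The sample size is described as "sufficient to detect a 9.4% absolute difference (hazard ratio = 0.87) in ITN attrition rate". That is all-cause attrition, a different endpoint, which the exclusion does not touch.
- *Four survey dates also push survival down or separate the arms.* Step 6 shows otherwise: the estimate at each visit is right, the median is read too late, and a schedule common to all arms creates no difference by itself.

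**Conclusion.** The point holds as a stated rule that should be changed or, if censoring was always meant, clarified. On the plain reading, 36-month functional survival is understated by 1.6 to 10.9 points for give-away shares of 10% to 70%, given 70% total attrition, constant hazards and give-away independent of wear. With identical wear, a false gap of 3.6 to 8.5 points arises if give-away risk is 10% in one arm and 30% to 50% in another. There is none if wear and give-away rates are equal across arms. Without independence, the sign of the bias is open. The late reading of the median from a step curve is a separate and minor matter.

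**What to change.** Replace the exclusion sentence with a rule that nets given away, sold or stolen stay at risk and are censored within the interval in which they were lost, using an actuarial mid-interval or interval-censored estimate. Avoid fixing the censoring at either bounding visit in the main analysis, since each adds a bias of its own (step 5).

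Report loss by cause for each net type, so that readers can see whether give-away differs. Add a sensitivity analysis in which giving away is related to wear. As a minor addition, obtain the median by interpolation or from the interval-censored fit.

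The cost is analysis wording. The surveys already record presence and reason for loss, and no date of loss is needed. The article reports surveys complete to 24 months, so the 36-month round was still to come, but the change asks for nothing extra from it. If censoring was the intention all along, the first change is a one-sentence clarification.

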### Study design

The study area was divided into 60 clusters that were randomly assigned to the three arms of the cRCT using restricted randomization. Study nets are identical in appearance and participating households are blinded to the type of ITN they received. Field data collectors are also blinded to the allocation of households to the study arms. Ten clusters from each study arm have been randomly selected for the durability assessment (Fig. 1). Following ITN distribution, households in these clusters will be visited to mark and prospectively follow 2 separate cohorts of ITNs per arm (Cohorts 1 and 2) every 6–12 months to monitor their physical and insecticidal durability over a period of 36 months. Cohort 1 will consist of at least 750 nets from ~ 250 randomly selected households per arm (assuming 3 ITNs are distributed per household) from 5 study clusters per study arm. These nets will be followed for ITN survivorship and fabric integrity at 6-, 12-, 24- and 36-months post ITN distribution. Cohort 2 will consist of ~ 1800 nets per study arm from ~ 600 households from all 10 randomly selected clusters (60 households per cluster) per study arm to be withdrawn (and replaced with new nets) for assessment of insecticidal activity in laboratory bioassays and experimental hut trials, content of each active ingredient and for other studies. Cohort 1 and cohort 2 nets will receive separate identification numbers and would be sampled from different households to prevent the risk of destructive sampling of nets intended for ITN survivorship studies (cohort 1). Figure 2 provides a summary of the study design and studies to be performed at each timepoint.

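### The cohort 1 comparisons of attrition, functional survival and hole area name no adjustment for cluster, although net type was allocated by cluster and the sample size section states an ICC of 0.03

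*Protocol article*

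**What the plan says.** Protocol article, Study design: "The study area was divided into 60 clusters that were randomly assigned to the three arms of the cRCT using restricted randomization". Cohort 1 is drawn "from 5 study clusters per study arm".

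Protocol article, Sample size calculations: the basis is "a sample size of 750 nets of each brand from 250 randomly selected households (assuming ~ 3 ITNs are distributed per household) in 5 study clusters". This is said to be enough to "detect a 9.4% absolute difference (hazard ratio = 0.87) in ITN attrition rate". The planning values behind that claim are 70% loss among control nets by year 3 and, for dependence within clusters, "an intra-cluster correlation coefficient of 0.03". No significance level or power is given for cohort 1; 80% power appears only for the hut trials.

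Protocol article, Statistical analysis: survey data will be used to "calculate attrition, functional survival and median survival time using Kaplan–Meier estimators". For fabric integrity, "Negative binomial regression will be used to compare hole surface area between the different ITN types". No cluster or household term, shared frailty, robust variance or cluster-level summary is named for either, and no test is named for comparing attrition between arms. The same paragraph does list hut, sleeper, net replicate and nightly error terms for the proportional outcomes of the hut trials.

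**The concern.** Nets in the same cluster share a net type and also local conditions that affect wear and loss. Nets in the same household (about 3) share still more. With 5 clusters per arm, the precision of a between-arm comparison is limited by variation between 10 clusters, not by 1,500 nets. An analysis that counts nets as independent overstates precision.

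The first objective compares survivorship, attrition and fabric integrity with Interceptor, and cohort 1 is sized to detect a difference in attrition, so a between-arm comparison is intended. The Discussion says that the results will inform replacement planning and procurement. The risk is that chance differences between a few clusters are reported as differences between net brands. Ordinary cluster-robust standard errors would not be a safe default, because they are unreliable with so few clusters per arm.

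**Working it through.** **Inputs.** From Sample size calculations: 750 nets per arm, 5 clusters, ICC 0.03, control attrition 70%, target difference 9.4 points. From the fabric integrity section: a minimum of 250 nets, read here as per arm, which the text does not say. Assumed: two-sided 5% level, 80% power, equal cluster sizes, and for hole area the attrition ICC, because none is given.

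**The plan's own figure.** For 70% versus 60.6%, without clustering:

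n = [1.96·√(2·0.653·0.347) + 0.842·√(0.7·0.3 + 0.606·0.394)]² / 0.094² ≈ 402 nets per arm.

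With m = 750/5 = 150, DEFF = 1 + 149 × 0.03 = 5.47, and 402 × 5.47 ≈ 2,199 nets per arm. The stated 750 is not reproduced with 5 clusters. It would fit a design effect of 750/402 = 1.87, that is, about 30 nets per cluster.

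**Attrition, net-level analysis.**
- Standard errors are too small by √5.47 = 2.34.
- False-positive rate = 2·[1 − Φ(1.96/2.34)] = 40.2%.
- Simulation under no difference (5 clusters of 150 nets per arm, four survey times): net-level log-rank 42.3%; t-test on cluster proportions 4.7%.
- Sensitivity: ICC 0.01 gives DEFF 2.49 and 21%; ICC 0.05 gives DEFF 8.45 and 50%.

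**Hole area, net-level analysis.** Only nets still present are measured.

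| Nets per arm | Per cluster | DEFF (ICC 0.03) | SE factor | False-positive rate |
|---|---|---|---|---|
| 750 | 150 | 5.47 | 2.34 | 40% |
| 250 | 50 | 2.47 | 1.57 | 21% |
| 225 (30% of 750) | 45 | 2.32 | 1.52 | 20% |

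Simulated negative binomial Wald tests give 41.5% at 150 nets per cluster and 23% at 50. At 250 nets per arm, an ICC from 0.01 to 0.10 moves the rate from 11% to 42%.

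**Precision once clustering is respected (attrition).**
- Effective size: 750/5.47 = 137 nets per arm.
- Power for 70% versus 60.6%: Φ[(0.094·√137 − 1.96·√(2·0.653·0.347)) / √(0.7·0.3 + 0.606·0.394)] = Φ(−0.33) ≈ 37%. If attrition is 9.4 points higher instead (79.4%), power is 43%.
- Detectable difference at 80% power: about 16.4 points.
- These are normal approximations. A t-test with 8 df is less favourable: SE = √[(0.21 + 0.2388)/137.1] = 0.0572, non-centrality 0.094/0.0572 = 1.64, critical value 2.306, power about 30%. At 80% power it detects about 18.5 points.

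**The case against.** The article names a regression family and an estimator in a sentence each, and covariance structure is often left to the full plan. Negative binomial regression can carry a random effect, and lme4, one of the two packages named, fits mixed models. The hut-entry count model is described just as briefly, although hut and sleeper effects are recognised elsewhere, so short wording is not proof of an intention to ignore clustering. This stands: the text omits the adjustment and does not rule it out. A reader might infer that the authors have chosen an unadjusted analysis; the document does not say so.

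A reader might also infer that the planned analyses have a 40% false-positive rate. That goes too far. Kaplan–Meier is an estimator, no attrition test is named, and the figure applies only if a net-level test is used. It should not be carried over to hole area at 36 months, where about 20% is nearer.

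Finally, a stated ICC need not mean that the sample size carries the full design effect, and the arithmetic suggests that it does not.

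What the objection does not remove is the mismatch: an ICC is stated at the planning stage and no allowance for it appears among the named cohort 1 methods, while dependence terms are spelled out for hut outcomes in the same paragraph. With 5 clusters per arm the choice of small-sample method matters, so a general intention to adjust would not settle it.

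**Conclusion.** The concern holds in a conditional form. The cohort 1 methods, as named, make no allowance for cluster or household in a cluster-allocated comparison. Run that way, intervals for attrition are too narrow by a factor of about 2.3, and a net-level test of attrition would reject falsely about 40% of the time, given ICC 0.03, equal clusters and nearly all marked nets contributing. For hole area the rate runs from about 40% early to about 20% at 36 months, on a borrowed ICC. Even the lower figure is four times the nominal 5%. The added effect of household clustering within cluster is not quantified here.

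**What to change.** State in the analysis plan that attrition, functional survival and hole area are compared between arms in one of two ways:
- cluster-level summaries, 5 versus 5, with a t-test on 8 df; or
- models with a random effect for cluster, household nested within it, and a small-sample degrees-of-freedom correction.

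State also that confidence intervals around the Kaplan–Meier estimates and median survival allow for clustering, and that unadjusted net-level p-values are not used for between-arm claims.

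No new data or field work is needed, but the change is not free. Intervals widen, and the 9.4-point target is no longer supported: power is about 37% by normal approximation (about 30% with 8 df), and the detectable difference at an assumed 80% power is about 16 points (about 18.5 with 8 df). The sample size section should restate the detectable difference, with its significance level, power and design effect, so that a non-significant result is not read as evidence of equal durability.
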